## 2. Objectives and Hypothesis

The general objective is to assess the impact of the application of acupressure on obstetric and neonatal outcomes of labor. To achieve the general objective, four specific objectives have been established, each based on the verification or refutation of a specific hypothesis.

Objective 1: To analyze the possible statistical association between the use of acupressure and the times of cervical dilation and fetal delivery.

Null hypothesis: The dilation time and the expulsive time in the women who receive the intervention is the same as those of the women in the control group.Alternative hypothesis: The time of dilation and the time of expulsion in the women who receive the intervention is not the same as those in the women in the control group.

Objective 2: To compare the pain perceived by pregnant women in relation to the use of the acupressure technique.

Null hypothesis: The pain experienced by women receiving the intervention is the same as that experienced by women in the control group.Alternative hypothesis: The pain experienced by women receiving the intervention is not the same as that experienced by women in the control group.

Objective 3: To study the relationship between the use of acupressure and maternal satisfaction regarding the childbirth experience.

Null hypothesis: The satisfaction experienced about the birth process in women receiving the intervention is the same as that in women in the control group.Alternative hypothesis: The satisfaction experienced about the birth process in women who receive the intervention is not the same as that in women in the control group.

Objective 4: Assess the safety of the intervention through fetal and neonatal outcomes.

Null hypothesis: The fetal and neonatal results of the pregnant women belonging to the intervention group are the same as those in the pregnant women of the control group.Alternative hypothesis: The fetal and neonatal results of the pregnant women who belong to the intervention group are not the same as those in the pregnant women of the control group.

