### 3.3. Sampling and Sample Size

The sampling process will be conducted using an intentional or convenience sampling approach, wherein all pregnant women who meet the inclusion criteria and are under the care of the project’s principal investigator will be included until the predetermined sample size is reached. This meticulous approach aims to encompass a diverse range of participants, thereby enhancing the generalizability of the study findings.

The calculation was based on the results obtained in a pilot study (unpublished data) with 17 and 23 women in the intervention and control groups, respectively, using the Gpower 3.1.9.4 software. Different calculations were carried out based on the means and standard deviations obtained in the times of the active, passive, and expulsive phases, as well as on the VAS scale (Likert 1–10 points) used to measure pain. From the different calculations carried out, the one that determined the largest sample size (difference of means in time of expulsive phase) was selected with the intention of having sufficient statistical power for all the analyses proposed.

The means and standard deviation obtained for the expulsive phase time (second stage of parturition, which starts at full dilation and continues until birth) in a pilot study were 46 ± 39 min for the intervention group and 65 ± 47 min for the control group. The number of women per group was calculated to determine a difference in the means of independent groups with alpha = 0.05 (type I error), power (1-beta) = 0.8, and allocation n1/n2 ratio = 1, obtaining a total of 166 women (83 in each group) [23].

Recruitment. The selection of participants for this study will adhere to specific criteria outlined as follows:

Inclusion criteria: The study will include pregnant women who meet the following requirements: Women with induced, accelerated, or spontaneous labor, both primiparous and multiparous, are included.Women who are 18 years of age or older and in the term of their pregnancy (37–42 weeks).Single gestation (not multiple pregnancies).Absence of associated pathologies or medical conditions.Proficient communication skills in the Spanish language.

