Exclusion criteria: The study will exclude pregnant women who meet any of the following criteria: Women with a fetus in a breech or transverse presentation.Women who have previously undergone caesarean sections.Women with existing skin lesions or wounds.Women with cognitive deficits or impairments.Women who have consumed toxic substances or medications during their pregnancy.Women with diagnoses of placenta previa (previous insertion placenta), fetal pathologies such as Delayed Intrauterine Growth (DIC) or Small for Gestational Age (SGA), or instances of oligo- or polyhydramnios.

These well-defined criteria will ensure that the study focuses on a specific group of pregnant women, enabling researchers to examine the intended effects of the intervention more accurately. 

Allocation. Assignment to the intervention group will be made by simple randomization of the sample. To do this, a random sequence of numbers will be generated using R software (R 4.1.3, March 2022), which is open source and specifically designed for statistical analysis, to assign women to intervention/control groups. For this purpose, the function will be used: sample (1:166, 83, replace = FALSE). The women who are attended in the order of arrival will be included in the intervention group if their order coincides with any of the random numbers generated.

Intervention. Intervention will be implemented by a single researcher and it will be based on pressure on the points detailed below:

It will start by exerting pressure on:-LI4 of the left hand, SP6 of the left leg, GB21 of the left shoulder, and then the same sequence on the right side. This is intended to generate regular and effective contractions and promote the descent of the fetal head.-Yongquan (R1): For pain relief and relaxation of women, exerting constant pressure for 1 min, as many times as necessary to promote pain control.-Hand points: Also for pain relief, autonomously by the woman, whenever she needs it.

The location of the trigger points can be visualized in Appendix A.

Constant pressure will be generated for 3 min, alternating points, and repeating the technique every 4 h, after the scans. Digital pressure will be applied until half of the nail turns white (equivalent to 3 to 5 kg of pressure) [23]. The Hegu point (LI4) will also serve as an analgesic point.

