The purpose behind administering pressure to different points using fingers in the control group is to eliminate any potential placebo effect associated with “manipulation using a therapeutic instrument”. It is important to note that none of the points pressed in either the intervention group or the control group possess an anatomical location that can induce significant physiological changes when pressure is applied, such as pressing the carotid artery. This precautionary measure ensures the safety of the study participants, minimizing any adverse effects resulting from the applied pressure on the women. Thus, the inclusion of these additional control points not only serves to rule out placebo effects, but also guarantees the well-being and welfare of the participants by preventing any unintended consequences arising from the pressure applied during the study.

Outcomes. Variables will be measured in order to assess the efficacy and safety of the intervention:-Effectiveness of the use of acupressure on labor times in minutes (time of cervical dilatation and time of fetal expulsion according to the recommendations of the World Health Organization).-Effectiveness of the use of acupressure on women’s perceived pain by recording values on the VAS scale and the need for pharmacological analgesic methods. A Visual Analogue Scale (VAS) is a pain rating scale that was first used in 1921 by Hayes and Patterson. The pain VAS is a one-dimensional measure of pain intensity that is used to record the progression of patients’ pain or to compare the severity of pain between patients with similar conditions. The patient must rate their perceived pain on a scale of 0 (no pain) to 10 (the most severe pain imaginable) [1,4,13,14,15,17,19,24,25,26].-Impact of the use of acupressure on maternal satisfaction expressed about the childbirth experience (using the validated satisfaction scale Mackey Satisfaction Childbirth Rating Scale—MSCRS) [8].-Impact of the use of acupressure on neonatal outcomes (Apgar test at 1/5/10 min and arterial blood gases at birth).

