Independent variables.-Sociodemographic: Age (years), country of birth, weight (kg), height (cm), marital status (single, domestic partner, married, divorced, widowed), studies (primary, secondary, superior, postgraduate), employment (employed, unemployed), dysmenorrhea: yes/no (verbalization by the woman of having painful menstruations), fear of childbirth (yes/no), reasons for fear of childbirth (verbalization by the woman), hospital (public/private).-Clinics: date of last period (FUR) and probable date of delivery (FPP), gestational age (weeks of gestation), obstetric formula (pregnancies, abortions, childbirth), estimated fetal weight (kg), fetal weight at birth (kg), type of delivery termination (eutocic, instrumented, caesarean section), special circumstances associated with childbirth (maternal fever, meconium, cord prolapse, antepartum hemorrhage, and uterine rupture), factors associated with the newborn (abnormal registration and altered arterial pH, considering normal values—arterial pH at birth: 7.25–7.45, blood oxygen (PaO2): 60–80 mmHg, blood carbon dioxide (PaCO2): 35–45 mmHg, bicarbonate (HCO3-): 24–26 mEq/L, base excess: ±3.0).-Variables that can affect the effectiveness of the intervention: hospital shift the night before (yes/no), start time of application of the technique (0–24 h), level of saturation of the system (number of women in the service attended by the researcher).

Data analysis. The data obtained will be analyzed with IBM SPSS Statistics v23 software; this will allow for the descriptive analysis of qualitative variables through absolute frequencies and percentages, and of quantitative variables through measures of central tendency, dispersion, and position. On the other hand, a statistical inference analysis will be carried out to evaluate the possible differences between the groups; these will be treated as unpaired samples because there are different women who constituted each group.

The statistical association between qualitative variables will be analyzed using Pearson’s chi-square test or Fisher’s exact test (in 2 × 2 tables when in Pearson’s Chi square, the expected frequencies are less than 5 in more than 20% of the cells). Odd ratio will be calculated as size effect measure for this analysis.

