For the comparison of means between dichotomous variables, the Student t-test and ANOVA test will be performed in the case of dichotomous or polytomous variables, respectively, as long as the parametric criteria are met (normality evaluated using the Kolmogorov–Smirnov test and homoscedasticity evaluated with the Levene test). If the parametric criteria are not met, non-parametric tests will be performed (Wilcoxon test and Kruskal–Wallis test, respectively). For the Student t-test analysis, Cohen’s d will be used as a measure of the effect size. 

For regression analysis, the Pearson correlation coefficient will be used. In the case of non-normal distributions, Spearman correlation test will be used. Statistical significance at 5% will be established for all tests.

Ethical aspects. The present study preserves the well-being of the subject above the interests of science or society and the ethical considerations that support it, as part of the compliance with current international and national regulations for health research studies with human beings, as well as that referring to the protection of personal data and clinical information derived from it. Under these premises, this protocol has been approved by the Regional Ethics Committee (committee code 4928, project code: AcuP, approval date 24 February 2021, record number 319).

Data collection notebooks will be handled in which only identification codes will appear that will correspond to the personal data in other guarded records. Similarly, electronic database-type records will be designed disaggregated to avoid identification of patients. An Informed Consent document has been prepared. The intervention does not require invasive tests or manipulation of biological samples beyond those implemented in routine clinical practice.

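### Dilation time is compared as a completed duration by t-test or Wilcoxon, but a woman delivered by caesarean before full dilation has none; omitting her or entering a cut-off time can both distort Objective 1

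*Protocol article*

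**What the plan says.** All references are to the protocol article.

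- **Hypothesis (section 2, Objective 1).** The null hypothesis is that "The dilation time and the expulsive time in the women who receive the intervention is the same" as in the control group. The alternative is two-sided.
- **Endpoint (section 3.3, Outcomes).** Labour times in minutes: "time of cervical dilatation and time of fetal expulsion according to the recommendations of the World Health Organization".
- **Where dilation ends (section 3.3, sample size).** The expulsive phase is the "second stage of parturition, which starts at full dilation and continues until birth". The dilation stage therefore ends at full dilation.
- **Test (section 3.3, Data analysis).** "For the comparison of means between dichotomous variables, the Student t-test and ANOVA test will be performed" when the parametric criteria hold. "If the parametric criteria are not met, non-parametric tests will be performed", with Wilcoxon named for two groups. No time-to-event method is named.
- **Caesarean (section 3.3).** The exclusion is "Women who have previously undergone caesarean sections", which concerns earlier births only. Caesarean in the index labour is recorded among the clinical independent variables, as one level of "type of delivery termination (eutocic, instrumented, caesarean section". No rule says what dilation time such a woman receives.

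**The concern.** The t-test and the Wilcoxon test each need one value per woman. A woman whose first stage ends in caesarean never reaches full dilation, so the endpoint is undefined for her. Eligibility covers induced labour and first births, so the case is foreseeable.

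There are two ways to run the stated test, and neither compares the randomised groups fairly.

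- **Leave her out.** Membership of the comparison then depends on an event after allocation. The article says the main points are pressed to strengthen and regularise contractions, so the intervention may influence that event. If slow labours are more often the ones that end in caesarean, and acupressure changes duration or the caesarean rate, the arms lose different shares of their slow labours.
- **Enter her time to caesarean as if dilation had been completed.** That time is a lower bound on her dilation time, and the arm with more such women is made to look faster than it is.

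The size of the effect on dilation time is at stake, and mostly in the direction of understating a real benefit.

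**Working it through.** **The plan's own figure.** The plan gives no dilation-time mean or SD and no caesarean rate. Its only related figure is the total of 166, from the expulsive phase. Pooled SD = √((39² + 47²)/2) = 43.19 and d = 19/43.19 = 0.44. The exact two-sided t-test at 80% power gives 83 per group (power 0.804). The 166 reproduces and is not in question here.

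**Assumed inputs (not in the documents).**
- Control dilation time T is log-normal with mean 300 and SD 180 min. On the log scale σ² = ln(1 + (180/300)²) = 0.3075, so σ = 0.5545.
- Acupressure multiplies every time by 0.9. The means are 300 and 270, a true difference of 30 min.
- Caesarean before full dilation occurs when a standard normal index exceeds c = Φ⁻¹(1 − p). Here p is the control caesarean rate and r is the correlation of the index with log T. In the intervention arm the index shifts by rδ, with δ = ln(0.9)/0.5545 = −0.190; in control δ = 0.

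**Formula.** The mean among women who reach full dilation is

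M × Φ(c − rδ − rσ) / Φ(c − rδ), where M is the arm's full mean. Setting r = 1 gives the hard cutoff, in which every labour beyond a fixed limit, and no other, ends in caesarean.

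**One case in full (r = 0.5, p = 10%, c = 1.2816).**
- Control: 300 × Φ(1.0043)/0.900 = 280.8 min.
- Intervention: 270 × Φ(1.0993)/Φ(1.3766) = 254.8 min.
- Difference 26.0 min against 30 true.

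**Difference among completers, true value 30 min.**

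| Link r | p = 5% | p = 10% | p = 15% |
|---|---|---|---|
| 0 | 30.0 | 30.0 | 30.0 |
| 0.3 | 28.9 | 28.2 | 27.6 |
| 0.5 | 27.4 | 26.0 | 24.9 |
| 0.8 | 24.0 | 21.2 | 19.2 |
| 1 (hard cutoff) | 21.0 | 17.1 | 14.5 |

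In the bottom-right cell the limit is 457 min, caesareans are 15.0% against 11.0%, and the completers' means are 241.8 and 227.3 min.

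**Entering time to caesarean as completed (hard cutoff, p = 15%).** Control: 0.85 × 241.8 + 0.15 × 457.0 = 274.1. Intervention: 0.89 × 227.3 + 0.11 × 457.0 = 252.6. The difference is 21.5 min, again short of 30.

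**No effect on duration, but fewer caesareans of slow labours (10% against 15%).** Under the hard cutoff, completers average 255.5 min with acupressure and 241.8 in control, so acupressure looks 13.7 min slower. With a partial link the same contrast is:
- r = 0.3: 289.2 − 285.1 = 4.1 min
- r = 0.5: 280.8 − 273.9 = 6.9 min
- r = 0.8: 266.3 − 255.3 = 11.0 min

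**No effect on duration or on caesareans.** Both arms lose the same share of the same distribution, so the difference stays at zero.

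**Second set of assumptions.** A separate simulation used mean 360, SD 200, a 15% shortening (true 54 min), r from 0.5 to 0.8 and 5 to 20% control caesareans. Completers showed about 33 to 50 min when caesarean depended on duration only, and about 17 to 45 min when acupressure also lowered caesareans directly.

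**The case against.** **The article never says these women are excluded.** This is right. A reader might infer that the plan drops them, but that follows only from the endpoint and the test. Entering time to caesarean would fit the text equally well. The objection removes the claim that the plan prescribes a completers' analysis. It does not rescue the plan, because the other way of running the test is also distorted.

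**The rule may sit in a fuller document.** How an event enters an endpoint is often left to the analysis plan, and an article condenses. Silence alone would not be a point. Here, however, the article names both a duration and a test on observed values, and together these have no defined result for a foreseeable group of randomised women. A rank test can accommodate a rule for them, but the first-line t-test has no sound value to use.

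**The bias may be small.** This stands in part. At r = 0.3 to 0.5 and 5 to 15% caesareans it is about 1 to 5 min. The standard error at 83 per arm, under the same assumptions, is √((180² + 162²)/83) = 26.6 min. Nothing in the documents gives the caesarean rate or ties caesarean to slow progress.

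**Two stronger readings fail.** A reader might infer that a true shortening could turn into apparent harm. In every scenario run with a true shortening the sign holds; reversal appears only where duration does not change and caesareans of slow labours fall. A reader might also look for a contrast with the scoring of operative births in the second stage, but the article gives no scoring rule for those either.

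**Conclusion.** The point holds as a badly fixed analysis. Objective 1 commits to a t-test or Wilcoxon on dilation minutes, while the same article foresees women who cannot have that value. Both ways of running the test on the available numbers can distort the comparison.

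The size depends on assumptions that the documents cannot settle. For a true 30 min shortening, the completers' difference is about 19 to 29 min over the partial-link range and about 14.5 min at the extreme. There is no distortion if caesarean is unrelated to duration, or if acupressure changes neither. In the shortening scenarios the error understates the benefit. It would favour acupressure if acupressure raised caesareans among slow labours. The rule should be settled before the data are analysed.

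**What to change.** Replace the main dilation analysis with one that keeps every randomised woman:

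- **Main analysis:** time to full dilation, with caesarean before full dilation as a competing event (cumulative incidence by arm, or a cause-specific hazard comparison).
- **Sensitivity analysis:** the Wilcoxon test already named, with women delivered by caesarean before full dilation given the worst rank.
- **Alongside:** the number of first-stage caesareans by arm, with completed minutes among women who reached full dilation as descriptive only.

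**Cost.** This is mainly analysis wording, since delivery type is already recorded. The article does not list the time of the caesarean or whether full dilation had been reached. If the data collection notebook lacks these, they must come from the labour record. The main result is then no longer a simple difference in mean minutes. Worst rank also penalises caesareans done for reasons other than slow progress, such as the cord prolapse or antepartum haemorrhage that the article lists, which is why it is better kept as a sensitivity analysis.

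### Labour times are compared by an unadjusted test chosen by pre-tests on the outcome; one pre-specified parity-adjusted analysis would fix the effect measure and gain precision

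*Protocol article*

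**What the plan says.** All places are in the Protocol article.

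- **Who enters** (section 3.3, Recruitment): "Women with induced, accelerated, or spontaneous labor, both primiparous and multiparous, are included".
- **Allocation** (section 3.3): simple randomisation from a random list of 83 out of 166 positions, with no stratification.
- **Parity** (section 3.3, Independent variables): the clinical variables include "obstetric formula (pregnancies, abortions, childbirth", so parity is recorded.
- **Sizing** (section 3.3): the number of women was "calculated to determine a difference in the means of independent groups", from a pilot expulsive time of "46 ± 39 min for the intervention group and 65 ± 47 min for the control group", with "alpha = 0.05 (type I error), power (1-beta) = 0.8, and allocation n1/n2 ratio = 1". The result is 166 women, 83 per group.
- **Analysis** (section 3.3, Data analysis): Student's t-test is used if normality (Kolmogorov-Smirnov) and equal variances (Levene) hold. Otherwise: "If the parametric criteria are not met, non-parametric tests will be performed", which for two groups means the Wilcoxon test. Cohen's d is the effect measure for the t-test; none is named for the Wilcoxon test.
- **Regression** (same place): "For regression analysis, the Pearson correlation coefficient will be used", with Spearman's coefficient for non-normal data. No model of labour time on arm and covariates appears.

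**The concern.** Two features of the stated method deserve attention.

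**The analysis is chosen by the outcome data.** Depending on two pre-tests, the trial reports either a difference in mean minutes with Cohen's d, or a rank comparison with no stated effect measure. The sizing concerns a mean difference. If the pilot already shows that normality is unlikely, the article can foresee that the test it was sized on will often be set aside, yet it does not say what would then be estimated.

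**The comparison is unadjusted.** Women with and without previous births are mixed. If labour length depends on parity, the variation that parity explains stays in the error term, although the variable needed to remove it is already on the form.

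At stake are the clarity of the result for the outcome that sized the trial, and precision that costs no extra women.

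**Working it through.** **1. The plan's own figure.** Inputs: means 46 and 65 min, SDs 39 and 47, alpha 0.05, power 0.80, 1:1. The test is taken as two-sided because of the form of the alternative hypothesis: "The time of dilation and the time of expulsion in the women who receive the intervention is not the same".

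- Pooled SD = √((39² + 47²)/2) = √1865 = 43.19
- d = 19/43.19 = 0.440
- Normal approximation: n = 2(1.960 + 0.842)²/0.440² ≈ 81.1, so 82 per arm. The exact noncentral t calculation gives 83 per arm, with power 0.804.

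The stated 166 is reproduced. The sample size is correct for a t-test.

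**2. Skew.** Time cannot be negative. Normal curves with the pilot figures would give

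- Φ(−46/39) = Φ(−1.18) = 0.119 below zero in the intervention group
- Φ(−65/47) = Φ(−1.38) = 0.083 below zero in the control group

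Right skew is therefore strongly implied. It is inferred from the ratio of SD to mean, since no pilot distribution is shown.

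**3. What the gate does.** Simulation of 3,000 trials per case, 83 per arm, with times matched to the pilot means and SDs (planned effect). The shapes are assumptions. The article does not say whether the Kolmogorov-Smirnov test is corrected for estimated parameters (Lilliefors), so both forms are shown.

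| Shape | t-test used, Lilliefors | t-test used, uncorrected | Power, t | Power, rank-sum | Power of whole rule (Lilliefors / uncorrected) |
|---|---|---|---|---|---|
| Gamma | 0.000 | 0.199 | 0.812 | 0.873 | 0.873 / 0.859 |
| Lognormal | 0.000 | 0.037 | 0.815 | 0.956 | 0.956 / 0.953 |
| Weibull | 0.001 | 0.252 | 0.806 | 0.838 | 0.838 / 0.827 |
| Normal | 0.601 | 0.661 | 0.808 | 0.795 | 0.802 / 0.803 |

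Even normal data reach the t-test in only 60-66% of trials, because Levene's test often rejects with SDs of 39 and 47.

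With no effect and skewed data, the t-test is used in 0.1-2.1% of trials (Lilliefors) or 12-63% (uncorrected). Type I error of the whole rule is 0.037-0.051.

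**4. What parity could give.** The documents do not say how much of the variance in labour time parity explains, so R² is an assumption. With R² removed from the error variance, d becomes 0.440/√(1 − R²), at 83 per arm:

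| R² (assumed) | d | Power |
|---|---|---|
| 0 | 0.440 | 0.804 |
| 0.10 | 0.464 | 0.844 |
| 0.20 | 0.492 | 0.883 |
| 0.30 | 0.526 | 0.920 |

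A simulated parity mixture points the same way. It assumes half the women nulliparous, with a mean time 1.5, 2 or 3 times that of the others (R² 0.08, 0.21, 0.48). Power was about 0.86 for the unadjusted t-test, 0.81-0.83 for the rank test, and 0.89, 0.93 and 0.99 for linear regression on arm and parity. This set-up scales the intervention SD with its mean (about 33 instead of 39), so only the relative gain should be read from it.

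**The case against.** **The fallback is no weaker.** This stands. With skewed times matched to both pilot SDs, the rank test has more power than the t-test. In the parity mixture it falls below the t-test but stays above 80%. A reader might infer that the pre-test costs power or inflates false positives; the figures do not support that.

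**How rarely the t-test is used depends on the form of the pre-test.** This stands. A reader might infer that the t-test would hardly ever be used. That holds only with the Lilliefors correction, which the article does not mention. Uncorrected, the share under the planned effect is about 4-25%, and with no effect it can exceed half.

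**Chance imbalance is not bias.** This stands. If half the women are nulliparous (assumed), the stated list leaves a parity difference of 10 points or more in about 21% of trials. That is ordinary random error, already covered by the standard error of an unadjusted test. Adjustment improves efficiency; it does not repair an invalid comparison.

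**An unseen analysis plan may adjust, and medians can be reported.** This stands in part. The article lists covariates and mentions regression, and its descriptive statistics allow medians and quartiles in minutes. But it fixes the selection rule, describes regression only as a correlation, and names no effect measure with an interval for the rank test. The point concerns what is stated, not what is left out.

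**Conclusion.** The point holds as an improvement that should be made. It is not a threat to validity: the sample size is right, type I error stays near 5%, and power is near or above 80% in every case examined. Two things are lost.

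- **A fixed effect estimate.** Under the planned effect and skewed times, most trials would end in a rank test without a named effect measure, although the trial was sized on a difference in mean minutes. This rests on skew inferred from the pilot SDs and on assumed shapes.
- **Precision.** If parity explains 10, 20 or 30% of the variance, adjustment lifts power from about 80% to about 84, 88 or 92% at the same 166 women. The size of this gain rests wholly on the assumed R². It comes from using parity, not from avoiding the rank test.

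**What to change.** - Drop the Kolmogorov-Smirnov and Levene gate for labour times.
- Name one analysis of expulsive time in advance: linear regression of time in minutes on arm and parity (0 v 1 or more previous births), with robust standard errors, reporting the adjusted difference in minutes with 95% CI. This keeps the scale on which the trial was sized.
- Use the same model for dilation time.
- Give a log-time model (ratio of geometric means) and the rank-sum test as sensitivity analyses.
- Hospital type is optional. Section 4 reports 95% of women so far in a private hospital; if that share held, about 8 of 166 (0.05 × 166) would be public, so adjustment would add little.
- Add labour onset only if it is recorded at inclusion in all three categories of the eligibility criteria (induced, accelerated, spontaneous). It is not in the listed variables, so this would need an addition to data collection.

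**Cost.** For the core change, analysis wording only: parity is already collected and no more women are needed. The analysis is slightly more complex, and the effect is read conditional on parity. The change should be made before any comparison by arm. It does not settle how women who deliver by caesarean without a completed expulsive phase are handled; that question arises equally for the t-test and the rank test.
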